Coronavirus is a type of single-stranded positive-strand RNA virus with an envelope [8]. Currently, there is no specific therapy for coronavirus infections. Only a limited number of treatment studies have been conducted because most human coronavirus strains cause self-limiting disease and care is supportive. However, after the severe acute respiratory syndrome (SARS) coronavirus was identified in 2002 and caused a large global outbreak, there was an increased interest in the development of specific therapeutic agents. SARS-CoV case-patients were treated with corticosteroids, chloroquine phosphate, hydroxychloroquine, convalescent plasma, and lopinavir or ritonavir, and, except for ribavirin, many of these agents have in vitro preclinical data that support their efficacy [9–19]. Since the SARS outbreak, new therapeutic agents targeting viral entry proteins, proteases, polymerases and methyltransferases have been tested; however, none of them has been shown to be efficacious in clinical trials [20–22].

There are reports about the potential value of a number of drugs [9–12, 23]. Of the various therapeutic interventions that have been suggested as being potentially effective, chloroquine stands out as an attractive option for the treatment of COVID-19 in Nigeria, if found to be efficacious. It has been used extensively for the treatment of malaria in Nigeria and is low-cost. Clinically, it has been reported that chloroquine improves outcomes in patients with COVID-19 [24–26]. However, robust clinical trials are still required to prove their effectiveness and safety in the treatment of COVID-19 due to limitations in the design of reported clinical studies. Furthermore, there are recent reports of chloroquine poisoning following announcements of its potential effectiveness in the treatment of COVID-19 [27]. This compelled a notice by the Nigeria Centre for Disease Control (NCDC) publicly stating that chloroquine is not an approved treatment for COVID-19 [28].

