Chloroquine has been used clinically since 1944, primarily for the prevention and treatment of malaria [29]. More recently, it has been shown to have antiviral activity against HIV-1, avian influenza H5N1, HCoV-229E, hepatitis B and herpes simplex type 1 viruses [29–32]. Chloroquine’s anti-SARS-CoV activity involves a variety of mechanisms that inhibit virus replication such as suppressing phosphatidylinositol binding clathrin assembly protein (PICALM), inhibiting endosomal acidification required for virus/cell fusion and reducing terminal glycosylation of angiotensin-converting enzyme 2 (ACE2) receptors [31, 33, 34]. Chloroquine also suppresses tumour necrosis factor alpha and interleukin 6, which mediate the inflammatory complications of viral infection [29].

The inhibition of infection at the cellular level has been shown to occur at a 50% inhibitory concentration (*IC50*) of 8.8 ± 1.2 μM for SARS-CoV [31] and 50% maximal effective concentration (*EC50*) of 1.13 μM for SARS-CoV-2 [9]. Furthermore, an *EC90* of 6.9 μM was achieved for SAR-CoV-2 [9]. These findings are significant because they suggest that therapeutic doses needed for effective anti-SARS-CoV-2 activity are similar to doses used in the treatment of malaria, which is endemic in Nigeria, and rheumatoid arthritis [31, 35]. Hydroxychloroquine has not been studied to the same extent, but it appears to have more potent in vitro efficacy [36]. These concentrations of chloroquine are significantly lower than the 50% cytotoxic concentration (*CC50*) which ranged from greater than 100 μm to 261.3 ± 14.5 μm with selectivity index from 30 to more than 88 [9, 31].

Despite the promising results from in vitro studies, chloroquine has not been shown conclusively to be efficacious in the treatment of COVID-19. However, it is now part of the recommendations for treatment in several countries while awaiting results of planned and on-going clinical trials [23, 36]. These recommendations have been informed by two main sources—an expert consensus on chloroquine phosphate for treatment of COVID-19 from China and a clinical study undertaken in France [26, 37]. These and one other small study reported from China suggest that chloroquine and hydroxychloroquine prevent the worsening of pneumonia, facilitate the clearance of the virus and shorten the duration of COVID-19 [24–26, 37].

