There are very few clinical studies on the efficacy of chloroquine phosphate or hydroxychloroquine sulphate. In the main study that has generated expectations of a cure, hydroxychloroquine appeared to lead to a rapid decline in nasopharyngeal viral load with negative viral cultures in almost all patients at day 5 [26]. The duration of hospital admission was also short averaging 5 days. Although impressive, this evidence is considered weak [23], due to the methodological design of the study which had a small sample size and no control group.

Similar to chloroquine phosphate and hydroxychloroquine sulphate, there are few clinical studies investigating the effect of lopinavir/ritonavir in the treatment of COVID-19 disease [38]. The combination of antiviral serum protease inhibitors lopinavir and ritonavir has been touted as a potential therapy for COVID-19 disease. Both drugs have historically been used to manage human immunodeficiency disease type 1 (HIV-1) and found to have an in vitro inhibitory effect on the SARS-CoV virus [11, 23, 39, 40]. The antivirals work synchronously with ritonavir which inhibits the enzyme cytochrome P450 and by effect increases the plasma half-life of lopinavir [11].

Cao et al. [38] conducted an open-label randomized controlled trial in hospitalized patients using lopinavir/ritonavir in combination with standard care therapy. The study found that lopinavir/ritonavir in combination with standard therapy did not provide a clinical benefit or reduce mortality compared to standard therapy alone. However, the study was not blinded, meaning the knowledge of the assigned treatment could have biased the findings of the outcome assessors.

The relatively high morbidity associated with COVID-19 and potentially inappropriate use of publicized remedies means that identifying effective medications that can reduce the duration and severity of illness is a high priority globally. The World Health Organization is taking steps towards a multi-country clinical trial of potential therapeutic agents [41]. This study is being undertaken as part of global efforts to identify effective specific therapeutic agents for COVID-19.

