## Objectives {7}

To evaluate the clinical efficacy of chloroquine phosphate, hydroxychloroquine sulphate and lopinavir/ritonavir added on to standard therapy relative to standard therapy alone for treatment of individuals with laboratory-confirmed COVID-19
1.1.To evaluate the clinical efficacy of chloroquine phosphate added on to standard therapy relative to standard therapy alone for treatment of individuals with laboratory-confirmed COVID-191.2.To evaluate the clinical efficacy of hydroxychloroquine sulphate added on to standard therapy relative to standard therapy alone for treatment of individuals with laboratory-confirmed COVID-191.3.To evaluate the clinical efficacy of lopinavir/ritonavir added on to standard therapy relative to standard therapy alone for treatment of individuals with laboratory-confirmed COVID-19

The secondary objectives are:
To evaluate the effect of chloroquine phosphate, hydroxychloroquine sulphate and lopinavir/ritonavir added on to standard therapy compared to standard therapy on the rate of progression/resolution of COVID-19
1.1.To evaluate the effect of chloroquine phosphate added on to standard therapy compared to standard therapy on the rate of progression/resolution of COVID-191.2.To evaluate the effect of hydroxychloroquine sulphate added on to standard therapy compared to standard therapy on the rate of progression/resolution of COVID-191.3.To evaluate the effect of lopinavir/ritonavir added on to standard therapy compared to standard therapy on the rate of progression/resolution of COVID-192. To evaluate the safety of chloroquine phosphate, hydroxychloroquine sulphate and lopinavir/ritonavir added on to standard therapy compared to standard therapy in the treatment of individuals with laboratory-confirmed COVID-19
2.1.To evaluate the safety of chloroquine phosphate added on to standard therapy compared to standard therapy in the treatment of individuals with laboratory-confirmed COVID-192.2.To evaluate the safety of hydroxychloroquine sulphate added on to standard therapy compared to standard therapy in the treatment of individuals with laboratory-confirmed COVID-192.3.To evaluate the safety of lopinavir/ritonavir added on to standard therapy compared to standard therapy in the treatment of individuals with laboratory-confirmed COVID-19

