#### Exclusion criteria

An individual who meets any of the following criteria will be excluded from participation in this study:
ALT/AST > 5 times the upper limit of normalStage 4 severe chronic kidney disease or requiring dialysis (i.e. eGFR < 30)Pregnant or breast feedingAnticipated transfer to another facility which is not a study site within 72 hParticipants with known haematological diseases, e.g. G6PD deficiencyParticipants with chronic liver and kidney disease and reaching end-stageParticipants with arrhythmia and chronic heart diseaseParticipants known to have retinal disease or hearing lossParticipants known to have a mental illnessSkin disorders (including rash, dermatitis, psoriasis)Allergy to any study medication (4-aminoquinoline or lopinavir/ritonavir)

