## Relevant concomitant care permitted or prohibited during the trial {11d}

Non-supportive therapy prior to enrolment is permitted. Concomitant therapy for co-morbidities such as hypertension, diabetes, rheumatoid arthritis etc. will be permitted and documented. In addition, the list of participants’ medications will be assessed (from medical history) from at least 30 days prior to enrolment to the 15th day after enrolment.

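### Current or recent use of a study drug does not bar entry, so background exposure can dilute each comparison with placebo

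*Protocol article*

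**What the plan says.** Section {11d} of the protocol article covers permitted and prohibited care, but it prohibits nothing. On earlier treatment: "Non-supportive therapy prior to enrolment is permitted". On continuing treatment: "Concomitant therapy for co-morbidities such as hypertension, diabetes, rheumatoid arthritis etc. will be permitted and documented". It also provides that "the list of participants’ medications will be assessed (from medical history) from at least 30 days prior to enrolment to the 15th day after enrolment", but does not link that record to eligibility.

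The study drugs appear once in the Exclusion criteria {10}: "Allergy to any study medication (4-aminoquinoline or lopinavir/ritonavir". Neither the inclusion nor the exclusion list mentions current or recent use, and no washout is given. HIV infection and rheumatoid arthritis are not exclusions.

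Each primary sub-objective in Objectives {7} assesses a drug added to standard therapy "relative to standard therapy alone for treatment of individuals with laboratory-confirmed COVID-19". The Intervention description {11a} fixes dose and route and gives the control arm placebos of all three drugs. The analysis is by intention to treat, with no allowance for non-adherence {20c}. Section {31c} says the article is itself the full protocol.

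**The concern.** The trial asks what a drug adds to care that does not include it. A control participant who is already taking that drug resembles a participant in the active arm. A participant in the active arm who was already taking it gains less from allocation, and has two sources of a drug whose dose {11a} describes as fixed. Randomization balances such people between arms but does not restore the lost contrast.

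The protocol's own background makes exposure plausible. The Study rationale likens the doses expected to act on the virus to "doses used in the treatment of malaria, which is endemic in Nigeria, and rheumatoid arthritis", and rheumatoid arthritis is one of the conditions whose treatment {11d} lets continue. The rationale also notes that "there are recent reports of chloroquine poisoning following announcements of its potential effectiveness in the treatment of COVID-19", and describes lopinavir and ritonavir as drugs for HIV-1.

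At stake is the sensitivity of the trial. A drug that works could look less effective than it is, and the comparison of serious adverse events with control would be blunted in the same way. The protocol intends a negative result to redirect effort to other remedies, so a false negative would have consequences.

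**Working it through.** **1. Does any section close the gap?**

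| Section | What it does | Closes the gap? |
|---|---|---|
| Inclusion criteria | Consent, compliance, age, confirmed infection | No |
| Exclusion criteria | Study drugs named under allergy only; heart, retinal and skin disease excluded | In part: may remove some long-term users |
| Standard of care (Table 2) | Lists no study drug | No: does not govern other treatment |
| {11c} | Trial doses directly observed | No: concerns trial doses |
| {11d} | Permits earlier therapy and co-morbidity treatment; records medications | No |

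**2. The planned size.** Inputs from Sample size {14}: 200 per arm, odds ratio 2, 85% power, two-sided alpha 0.05, about 10% lost to follow-up. The proportional-odds formula for one 1:1 comparison is

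n per arm = 6(1.960 + 1.036)² / [(ln 2)² (1 − Σp̄³)] = 112.1 / (1 − Σp̄³),

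where p̄ are the category probabilities averaged over the two arms. The control distribution is not given, so 200 cannot be strictly reproduced. It is attainable: 200 × 0.9 = 180 evaluable needs 1 − Σp̄³ = 0.623, and an assumed control distribution with 65% in category 1 gives 179.05, hence 180 evaluable and 200 randomized. Other assumed distributions give 128 (even spread) to 225 (70% in category 1). I take the stated size and power as they stand.

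**3. Dilution.** Let f be the share of participants already exposed to the drug in a given comparison. No figure is given, so f is an assumption. As a worst case, exposed participants contribute no contrast:

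- Odds ratio = 2^(1−f)
- Power = Φ[(1 − f)(1.960 + 1.036) − 1.960]
- Evaluable per arm to restore 85% power = 180/(1 − f)², rounded up, then divided by 0.9 and rounded up

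| f | Odds ratio | Power | Randomized per arm to restore 85% |
|---|---|---|---|
| 0 | 2.00 | 85% | 200 |
| 1% | 1.99 | 84.3% | 205 |
| 5% | 1.93 | 81.2% | 223 |
| 10% | 1.87 | 76.9% | 248 |
| 20% | 1.74 | 66.9% | 314 |

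For example, at f = 10%: 2^0.9 = 1.87, and 0.9 × 2.996 − 1.960 = 0.736, so power is Φ(0.736) = 76.9%.

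**4. Check on the model.** Mixing category probabilities directly (control distribution with 65% in category 1; a share f of controls given the active-arm distribution) yields cumulative odds ratios of 1.94 to 1.95 at 5%, 1.88 to 1.90 at 10% and 1.77 to 1.80 at 20%. These are close to the table and slightly milder.

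**The case against.** A reader might infer that {11d} lets a control participant go on self-treating with chloroquine. It does not say so. Its first sentence covers therapy before enrolment only; continuing treatment is permitted only for co-morbidities. Someone who took chloroquine earlier that week may enter, but nothing permits them to carry on. The person on lopinavir/ritonavir for HIV is reached only through the open-ended list of conditions. The person with rheumatoid arthritis is closest to the text, and even there permission for the study drug is inferred, because {11d} names no drug.

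A reader might also infer that exposure is common. The background does not show that: it speaks of past or historical use, gives no count of poisonings, and compares doses rather than prevalence. At 1% the loss is under one point of power.

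The model is also a worst case. A control participant who took some chloroquine before admission still differs from one given the full observed course. Exposure is drug-specific as well, so one value of f does not apply to all three comparisons. Medications are recorded, and some exclusions remove some long-term users.

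All of this stands, and it limits the size of the problem. It does not remove the gap: enrolment of current or recent users is open as written, and no stated rule handles them.

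**Conclusion.** The point holds as a weakness in eligibility. As written, a person already taking a study drug can be enrolled and randomized to placebo or to that same drug, which pulls the comparison toward an odds ratio of 1.

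Type I error is unaffected: if a drug has no effect, balanced background exposure creates no difference. The cost is lost sensitivity. The document does not support calling that loss large. It is negligible near 1% exposure, about 4 points of power at 5%, 8 at 10% and 18 at 20%, all assuming no contrast in exposed participants; use that has stopped would cost less. With the frequency unknown, this should be fixed, but it is not grounds for holding the trial invalid.

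**What to change.** 1. **Eligibility.** Add to the Exclusion criteria {10} current or recent use of chloroquine, hydroxychloroquine or lopinavir/ritonavir, as recorded in the medication history that {11d} already collects from at least 30 days before enrolment.
2. **Consistency.** Reconcile {11d} with the fixed-dose and placebo-control description in {11a}, so that it is clear how study drugs from outside the allocated pack are handled. The clinical rule is for the sponsor to set.
3. **Participants already enrolled.** Flag pre-enrolment exposure from the recorded list, blind to allocation, and report the primary comparison without these participants as a sensitivity analysis. Only the pre-enrolment part of the record should be used: it is fixed at baseline, so excluding on it does not break the randomization, whereas medication taken afterwards could depend on allocation. The intention-to-treat analysis stays primary.

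The cost is one eligibility line, a clarification and one added analysis on data already collected. Some eligible patients are lost, including a few who would have been informative for the other drugs. If exposure is rare the loss is small; if it is common, so is the dilution avoided.

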## Trial design {8}

This is a multi-centre, randomized, double-blind, placebo-controlled multi-arm clinical trial with a parallel group and superiority design. There are three treatment arms and one control arm with equal distribution of participants between the arms. If the intervention drug for any arm is not available, then participants will be allocated equally to each of the available arms.

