## Intervention description {11a}

The dose and route of administration of the trial drugs are fixed. The medications will be taken with food. Missed doses for the day will not be made up. All intervention medications will be administered with the standard of care.

### Arm 1

In the chloroquine phosphate arm of the study, participants will receive chloroquine phosphate two 250mg tablets orally twice a day (12h/24h) for 7 days, two hydroxychloroquine placebo tablets orally twice a day (12h/24h) for 7 days and two lopinavir/ritonavir placebo tablets orally twice a day (12h/24h) for 14 days.

### Arm 2

In the hydroxychloroquine arm, participants will receive hydroxychloroquine sulphate two 200mg tablets orally twice a day (12h/24h) for 7 days, two chloroquine placebo tablets orally twice a day (12h/24h) for 7 days and two lopinavir/ritonavir placebo tablets orally twice a day (12h/24h) for 14 days.

### Arm 3

In the lopinavir/ritonavir arm, participants will receive two tablets of lopinavir 200mg/ritonavir 50mg combination tablet orally twice a day (12h/24h) for 14 days, two chloroquine placebo tablets orally twice a day (12h/24h) for 7 days and two hydroxychloroquine placebo tablets orally twice a day (12h/24h) for 7 days.

### Arm 4

In the control arm of the study, participants will receive two chloroquine placebo tablets orally twice a day (12h/24h) for 7 days, two hydroxychloroquine placebo tablets orally twice a day (12h/24h) for 7 days and two lopinavir/ritonavir placebo tablets orally twice a day (12h/24h) for 14 days.

If any of the treatment arms is not available, the placebo for the relevant drug will not be administered to participants in the other arms.

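### Concomitant medication is permitted without exception, with no interaction check or exclusion, although one blinded arm receives ritonavir, which the protocol itself calls a cytochrome P450 inhibitor

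*Protocol article*

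**What the plan says.** The heading of item 11d covers both permitted and prohibited care, but its three sentences only permit or record. On earlier treatment: "Non-supportive therapy prior to enrolment is permitted". On co-morbidities: "Concomitant therapy for co-morbidities such as hypertension, diabetes, rheumatoid arthritis etc. will be permitted and documented". On the medication list, it says that participants' "medications will be assessed (from medical history) from at least 30 days prior to enrolment to the 15th day after enrolment". No drug or class is barred, cautioned or made conditional.

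The exclusion criteria cover organ disease, pregnancy and breast feeding, anticipated transfer, several other disease groups and one item that concerns medication: "Allergy to any study medication (4-aminoquinoline or lopinavir/ritonavir". None concerns what else the patient is taking.

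The study rationale describes "ritonavir which inhibits the enzyme cytochrome P450 and by effect increases the plasma half-life of lopinavir". The intervention description (item 11a) says "The dose and route of administration of the trial drugs are fixed", and for Arm 3 that "participants will receive two tablets of lopinavir 200mg/ritonavir 50mg combination tablet orally twice a day (12h/24h) for 14 days". Items 16b and 17a keep participants, care providers and outcome assessors blinded.

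**The concern.** The protocol recognises that ritonavir changes exposure to a drug given with it; that is its stated role in the combination. The concomitant-care section then opens the door to other medicines in general terms without taking account of that effect. Because the care team is blinded, it cannot tell which participants are receiving the inhibitor.

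At stake is the safety of a participant who takes a medicine affected by the inhibition and is allocated to Arm 3. The point does not bear on the sample size, the type I error rate or the primary analysis.

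**Working it through.** The plan gives no figure to reproduce here, so the check is a comparison of what each section provides.

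1. *Could an affected patient be enrolled?* Yes. The exclusion list has no co-medication item. Some exclusions (arrhythmia, chronic heart disease, known mental illness, known haematological disease, advanced liver or kidney disease) will remove some people on long-term medicines. They do not remove the three co-morbidities that item 11d names as examples.

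2. *Could that patient continue the medicine?* Yes. Item 11d permits it, with an open-ended list of examples.

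3. *Is there an opportunity to notice before randomization?* Yes. The medication list is drawn from the medical history, and Table 4 places that history at screening, ahead of the baseline column that holds randomization and the first dose. What is missing is an instruction on what to look for and what to do.

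4. *Does another rule supply the action?*
   - The hold and stop rules in item 11b depend on creatinine clearance, ALT/AST and bilirubin only.
   - ECGs are scheduled at baseline and on days 3, 5, 8, 11–14, 15 and 29. They can reveal a problem once dosing has begun, but no interaction rule is tied to them.
   - The safety assessments section makes a study physician responsible for trial-related medical decisions but states no rule on interactions.
   - Item 17b prepares emergency unmasking for serious adverse events and SUSARs, which is after harm.

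5. *How many participants?* The design section says: "There are three treatment arms and one control arm with equal distribution of participants between the arms". The share allocated to ritonavir is therefore 1/(3 + 1) = 1/4, and the share not allocated to it is 3/4. If *p* is the proportion of enrolled patients taking an affected medicine without adjustment, the proportion of all participants exposed to the interaction is *p* × 1/4. The protocol does not give *p*, so this can lie anywhere from 0 (*p* = 0) to 25% (*p* = 1). That range is too wide to inform, so no participant count is derived.

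**The case against.** The strongest reply is that the harm is not in the document. The rationale presents P450 inhibition as the purpose of the combination, not as a hazard to other medicines, and no section says that any drug for hypertension, diabetes or rheumatoid arthritis is affected. This stands as a limit on size. It does not remove the point, because the protocol states both that the enzyme is inhibited and that the exposure of a co-administered drug rises as a result. A check for other affected medicines follows from those statements alone.

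A second reply is that a journal article condenses a fuller document, which may hold an interaction list. The trial status section does say that the protocol is accessible on the registry, and some definitions used in the article are not given there. But the data-access section says that the article is the full protocol. Item 11d also does not stay silent: it addresses this subject and settles it as unqualified permission.

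Third, clinicians may stop, substitute or adjust a medicine on their own judgement, and participants are closely observed. Both are true. The plan allows the exposure; it does not require it.

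A reader might be tempted by three stronger readings that the text does not support:

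- *That the plan contradicts itself.* It does not; permitting co-morbidity treatment is compatible with the statement about ritonavir.
- *That medication is first looked at after randomization.* The treatment/management review row in Table 4 does start at baseline, but the medication list comes from the history taken at screening.
- *That participants will be harmed, or that a named class of medicine is unsafe here.* Nothing in the document establishes either.

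**Conclusion.** The point holds as a safety gap in what the protocol fixes. Co-morbidity therapy is permitted without exception, no action follows from the medication assessment, and no exclusion concerns co-medication, while one arm receives a stated P450 inhibitor blinded at a fixed dose for 14 days. The other safeguards give chances to notice a problem but supply no restriction or action before harm.

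The conclusion rests on two assumptions: that the article's description of itself as the full protocol is accurate, and that some patients at these sites take a medicine affected by the inhibition. The second cannot be checked from the document. The size of the risk is therefore unknown, and confidence is moderate. The change is worth making because it is cheap and the gap is avoidable, not because harm has been shown.

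**What to change.** While the lopinavir/ritonavir arm is open:

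1. Before randomization, check the screening medication history against a prespecified list of medicines with an important ritonavir interaction. The investigators set the list in advance.
2. Add an exclusion criterion: a patient whose listed medicine cannot safely be stopped, substituted or dose-adjusted for the 14-day treatment period is not randomized.
3. Qualify item 11d: during treatment, listed medicines are neither started nor continued unadjusted. Apply this identically in all arms, so that the rule does not reveal allocation. All four arms take lopinavir/ritonavir or its placebo for 14 days, so a common rule fits the existing schedule.

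The design and intervention sections allow for an arm being unavailable. If lopinavir/ritonavir is, the check is not needed for patients randomized from then on.

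The cost is protocol wording, a list and the use of a history already collected; no test or visit is added. The downside is that an unknown number of otherwise eligible patients are excluded or have a medicine changed. With four equal arms, on average 3 in 4 of them would not have received ritonavir. That cannot be avoided, because allocation is not known before randomization and is concealed afterwards.
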